### Sample Size

Two programs were used to determine sample size: (a) G^∗^Power3 (Faul et al., 2007) which prioritizes statistical power, and (b) SSS-CET (Software for Sample Sizes in Cost Effectiveness Trials) which uses a Bayesian approach (Sarker et al., 2013). Based on these analyses, a sample size of 176 participants per group was established (*N* = 352). However, it should be noted that previous investigations have proven that 150 participants are sufficient for a cost-effectiveness study (Rubio-Valera et al., 2013, 2015). Thus, the sample size established for this study is 150 participants per study group (*n* = 300).

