### Clinical Evaluation

Patients will be assessed at baseline, immediately after treatment finalization, and at 6 and 12 months post-treatment.

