### Statistical Analysis

#### Analysis of Clinical Effectiveness

This study will be conducted on an intention-to-treat basis. Both groups will be compared to verify that there are no significant between-group differences at baseline. For comparisons, the ANOVA method will be used for continuous variables and the Chi-square test for categorical variables. Subsequently, a repeated measurement of ANOVA, including all variables over time, will be performed to assess whether missing values respond to a random or non-random pattern. If the missing values are greater than 5% the Expectation Maximization (EM) will be used as a data imputation method, as recommended by the literature (Schlomer et al., 2010).

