#### Cost-Utility Analysis

Cost-utility analysis is a method of economic evaluation based on preferences or utilities rated by individuals; in other words, the value that an individual assigns to their health status. Thus, the economic evaluation depends on the social perspective of the individual, in which patients express preferences about their health. The EuroQoL-5D Questionnaire (EQ-5D – Spanish version) will be used for the cost-utility analysis. This is a generic QOL instrument consisting of five domains, as follows: mobility; anxiety/depression; pain/discomfort; daily activities; and self-care. These five domains are coded into five severity levels, as follows: no problems; slight problems; moderate problems; severe problems; extreme problems. In this way, 3125 distinct health states can be established. Health states enable us to obtain a population-based preference score per country (the EQ-5D index). The assigned values range from 0 (death) to 1 (perfect health). In addition, this index includes a VAS similar to a thermometer, which measures health from 0 (worst imaginable health state) to 100 (best imaginable health state) (Rabin et al., 2015).

Through the EQ-5D health questionnaire, we will calculate utility as QALYs using the Spanish fees described above.

Using these data, we will calculate the incremental cost-utility ratios, defined as the difference in mean costs divided by the difference in mean QALYS. Given that the duration of this study is only 12 months, neither costs nor outcomes are subject to discount. To obtain more precise cost-utility ratios, these ratios will be calculated by means of the bootstrapping method (a resampling method), which involves creating a large number of samples with replacement from the original sample data, thus allowing for a distribution that better resembles the actual distribution of the population from which the original data was drawn. In this way, the study will generate 1000 random samples which will be used to define the confidence intervals for the cost-utility ratios.

Missing-data analysis will be computed using Student’s *t*-test and chi-square tests. Variables included in the analysis will be severity level, gender, and age; this will allow us to ascertain whether unexpected missing data due to participant dropout are related to chance or not.

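### EM imputation of clinical outcomes above 5% missing, with no multiple draws or variance correction, either understates standard errors or shrinks the treatment effect, depending on whether arm is in the EM model

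*Protocol article*

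**What the plan says.** The missing-data rule is in the protocol article under Analysis of Clinical Effectiveness. The section opens with "This study will be conducted on an intention-to-treat basis". It then plans a repeated-measures ANOVA that "will be performed to assess whether missing values respond to a random or non-random pattern". The rule follows: "If the missing values are greater than 5% the Expectation Maximization (EM) will be used as a data imputation method". Both the trigger and the method are fixed. EM is the only imputation method named anywhere in the article.

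The Cost-Utility Analysis section has its own missing-data paragraph. It plans t-tests and chi-square tests on severity, gender and age to find out "whether unexpected missing data due to participant dropout are related to chance or not". It names no imputation method.

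On the design, Clinical Evaluation gives four time points: "Patients will be assessed at baseline, immediately after treatment finalization, and at 6 and 12 months post-treatment". The Sample Size section fixes the number randomized: "Thus, the sample size established for this study is 150 participants per study group". No expected dropout rate is given.

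**The concern.** EM by itself estimates means and covariances by maximum likelihood. Used to fill in data, it replaces each gap with one predicted value. A standard test on the completed file then counts that value as a real observation lying exactly on the regression line. The sample looks larger than it is, and its residual variance looks smaller.

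The result depends on whether treatment arm is in the EM model, which the article does not say:

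- **Arm in the model, or EM run by arm:** the effect estimate is sound when data are missing at random, but its standard error is too small and false positives rise.
- **Arm left out:** filled values in both arms are pulled towards a common prediction, so the error rate holds but the effect is diluted.

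These are alternatives and do not occur together. Neither gives both an unbiased effect and a valid standard error. The PHQ symptom scores concerned are among the main outcomes, and the trial is framed as a superiority comparison.

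A separate, smaller point is that the planned tests of missingness are expected to show more than they can.

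**Working it through.** **The plan's own figures.** The article gives no error rate, standard error or missing rate for the EM step, so there is nothing to reproduce directly. The one design figure is the calculated sample size: "Based on these analyses, a sample size of 176 participants per group was established". Its inputs are not stated. Assuming d = 0.30, two-sided 5% and 80% power, the normal formula 2(1.960 + 0.842)²/0.30² gives 174.4, so 175 per group, and the exact noncentral t gives 176 (power 0.801). This is a back-fit, but it makes 0.30 SD a reasonable reference effect.

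**Inputs.** From the article: 150 per arm and four visits. Assumed: missing rate m at 12 months, correlation between visits of 0.5 to 0.7, data missing completely at random (the mechanism kindest to the plan), and a two-sided 5% ANCOVA at 12 months.

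**Formula, arm in the EM model.** Take one follow-up predicted from baseline and arm, with residual variance σ².

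- True variance of the effect: about 2σ²/[n(1−m)], because only n(1−m) outcomes per arm were observed.
- Variance reported from the filled data: about 2(1−m)σ²/n, because the filled points have zero residual and are counted in n.
- Ratio of reported to true standard error: √[(1−m)(1−m)] = 1−m.
- Type I error: 2[1 − Φ(1.96(1−m))].

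**Type I error, arm in the model**

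| Missing | Formula | Simulation, one follow-up, corr. 0.5 | Simulation, four visits, corr. 0.5 / 0.7 | Simulation, four visits, corr. 0.6 | Multiple imputation, corr. 0.6 |
|---|---|---|---|---|---|
| 5% | 6.3% | – | about 7% / 6% | – | – |
| 6% | 6.5% | – | – | 5.9% | 4.8% |
| 10% | 7.8% | 8.1% | 7% / 8% | 8.2% | 4.9% |
| 20% | 11.7% | 12.3% | 11.5% / 8% | 10.9% | 5.6% |
| 30% | 17.0% | 16.8% | 15% / 13.5% | 13.7% | 4.7% |

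The simulations used 4,000, 1,000 and 2,000 trials per cell (left to right; the multiple-imputation column shares the last). Multiple imputation used 20 imputations and Rubin's rules. Running EM within each arm gave the same results as putting arm in the model.

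The four-visit results are mostly a little below the formula at 20% and 30% because earlier visits help to predict the missing one. The 8% at 20% missing and correlation 0.7 is partly simulation noise, as complete-case analysis in that cell rejected only 3.4%. In the four-visit runs the reported standard error was 0.81–0.87 of the true one at 20% missing and 0.72–0.74 at 30%.

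The choice of ANCOVA is not critical. A group-by-time test in repeated-measures ANOVA gave 10–12% at 20% missing and 18% at 30%.

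**Effect estimate, arm left out.** With one follow-up, a fraction m of outcomes carries almost no arm difference, so the estimate is about 0.30(1−m): 0.27, 0.24 and 0.21 at 10%, 20% and 30% missing. Simulation gave 0.27, 0.242 and 0.208. With four visits it gave about 0.25–0.26 at 20% and 0.23 at 30%. Type I error stayed near 5% (3.7–5.4%).

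**The missingness tests.** Comparing observed variables between completers and dropouts can reveal that missingness is not completely random. It cannot separate missing at random from missing not at random, because that turns on the values not seen. A non-significant result does not show that dropout is due to chance.

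**The case against.** The strongest reply is that the article is a condensed account. That EM means a single fill is an inference, and the EM model's contents and the unit to which 5% applies are details that a SAP may settle. This stands in part: the size of the harm, and which harm it is, are conditional. It does not remove the point, because the article commits to EM as the way to impute data and names nothing that would carry the imputation uncertainty.

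The second reply is that no dropout rate is given and that the Retention section plans email links, telephone contact and continued invitations after treatment is stopped. This also stands. Just above the trigger the error is only 6–7%; doubling needs about 20% missing and tripling about 30%. But the rule has no ceiling, and the last visit comes 12 months after a 24-week treatment period.

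Four stronger readings are tempting, and the text does not support them:

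- **Costs, utilities and the bootstrap.** A reader might infer that EM also fills costs and QALYs, and that the 1,000 bootstrap samples inherit the error. The EM sentence is in the clinical section, and the article does not say this.
- **Tests as decision rules.** A reader might infer that the missingness tests decide whether EM is used, or cause the variance error. The only trigger is the amount missing.
- **Intention to treat.** A reader might infer that the repeated-measures ANOVA drops incomplete cases from the main analysis. Its stated purpose here is to examine missingness, and it does not define the analysis population.
- **Optimistic results in every case.** With arm left out of the EM model, the error rate holds and the dilution works against a superiority claim.

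**Conclusion.** The point holds for the clinical outcomes. Followed as written and read naturally, the rule gives one of two faults:

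- **Arm in the EM model, or EM by arm:** type I error of about 6–7% just above the trigger, 7–8% at 10% missing, 8–12% at 20% and 14–17% at 30%.
- **Arm left out:** nominal type I error, but a true 0.30 SD effect estimated at about 0.24–0.26 at 20% missing and 0.21–0.23 at 30%.

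These figures rest on a single conditional-mean fill, assumed missing rates, correlations of 0.5 to 0.7, data missing completely at random and a 12-month ANCOVA. The direction of each fault is firm, but its size in this trial cannot be known from the article. The pattern tests are harmless as description but cannot support a conclusion that dropout is due to chance.

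**What to change.** Replace the 5% EM rule for the clinical scales with one of these, fixed before unblinded data are seen:

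- a mixed model for repeated measures on all observed data, with arm by time and baseline score as covariate, no prior imputation and no percentage trigger; or
- multiple imputation with arm in the imputation model, combined by Rubin's rules.

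In the simulations above, multiple imputation kept type I error at 4.7–5.6% from 6% to 30% missing. Both options still assume that data are missing at random.

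Keep the ANOVA, t-tests and chi-square tests of missingness as description only, and drop the statement that they show whether dropout is due to chance. If costs or QALYs are imputed at all, use multiple imputation by arm combined with the bootstrap, not a single EM fill.

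The cost is revised wording and somewhat more analysis work in standard software. Intervals will be wider than under a single fill with arm in the model, because they reflect what was actually observed. No extra patients, visits or data are needed.

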#### Description of Cost Analysis

Direct costs of health care will be estimated by adding the costs derived from medication use (antidepressants, hypnotics, sedatives, and anxiolytics), medical tests, use of health-related services, and staffing costs. The cost of medications will be calculated by determining the price per milligram (mg) during the study period according to the Vademecum International (Vidal, 2014), including value-added tax. Total costs of medications will be calculated by multiplying the price per mg by the daily dose (mg) and the number of days of drug treatment.

The main source of unit cost data related to public medical tests and use of health services will be obtained from the fee information published by the Official Government Journal of the Autonomous Community of Madrid (2013). Indirect costs will be calculated according to the number of days on sick leave multiplied by the minimum daily wage in Spain for 2015 (€21.62). Finally, total costs will be calculated by summing the total direct and indirect costs. The unit costs will be expressed in Euros (€) based on 2015 prices.

Currently, there is no reference fee for the TD-CBT intervention that will be used with the experimental group. The estimated cost of a consultation with a public sector GP in Spain is €39 (not including complementary tests). Given that salaries for psychologists in Spain are similar to those of GPs, we will use this amount (€39) to calculate the cost of the TD-CBT intervention (i.e., €39 multiplied by the number of assessment and treatment sessions, €39 × 9 = €351). Since the GP consultation fees are understood to include the cost of office space, we will not add any additional costs for office rent to the cost of the therapy. Accordingly, the total cost of the evaluation and psychological intervention (nine sessions) per person is estimated at €43.87 (€351/8).

#### Cost-Effectiveness Analysis

The cost-effectiveness analysis will be carried out by calculating the incremental cost-effectiveness ratios (ICER), defined as the difference in mean costs divided by the increase in effectiveness of the various therapeutic alternatives.

#### Cost-Utility Analysis

Cost-utility analysis is a method of economic evaluation based on preferences or utilities rated by individuals; in other words, the value that an individual assigns to their health status. Thus, the economic evaluation depends on the social perspective of the individual, in which patients express preferences about their health. The EuroQoL-5D Questionnaire (EQ-5D – Spanish version) will be used for the cost-utility analysis. This is a generic QOL instrument consisting of five domains, as follows: mobility; anxiety/depression; pain/discomfort; daily activities; and self-care. These five domains are coded into five severity levels, as follows: no problems; slight problems; moderate problems; severe problems; extreme problems. In this way, 3125 distinct health states can be established. Health states enable us to obtain a population-based preference score per country (the EQ-5D index). The assigned values range from 0 (death) to 1 (perfect health). In addition, this index includes a VAS similar to a thermometer, which measures health from 0 (worst imaginable health state) to 100 (best imaginable health state) (Rabin et al., 2015).

Through the EQ-5D health questionnaire, we will calculate utility as QALYs using the Spanish fees described above.

Using these data, we will calculate the incremental cost-utility ratios, defined as the difference in mean costs divided by the difference in mean QALYS. Given that the duration of this study is only 12 months, neither costs nor outcomes are subject to discount. To obtain more precise cost-utility ratios, these ratios will be calculated by means of the bootstrapping method (a resampling method), which involves creating a large number of samples with replacement from the original sample data, thus allowing for a distribution that better resembles the actual distribution of the population from which the original data was drawn. In this way, the study will generate 1000 random samples which will be used to define the confidence intervals for the cost-utility ratios.

Missing-data analysis will be computed using Student’s *t*-test and chi-square tests. Variables included in the analysis will be severity level, gender, and age; this will allow us to ascertain whether unexpected missing data due to participant dropout are related to chance or not.

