### Interventions

#### Experimental Group

The treatment program is included within a collaborative protocol of a stepped-care model of treatment, as recommended by the NICE (2011) guidelines. The first step involves group TD-CBT based on a treatment manual [Cordero-Andrés et al., 2017; González-Blanch et al., 2017; Cano-Vindel (Unpublished)]. The characteristics of this treatment have been described previously by Cano-Vindel (2011). EDs are believed to originate from a dual process of dysfunctional emotional learning over time that involves both cognitive (increasing use of cognitive distortions) and associative (classical conditioning in some significant emotional events) learning. Although this dysfunctional learning tends to lead to symptom chronicity and the development of new, comorbid disorders, the process is considered to be reversible. Moreover, both types of functional relearning (i.e., cognitive and associative) can be achieved with cognitive-behavioral techniques such as cognitive restructuring and behavioral exposure. A transdiagnostic approach (Newby et al., 2015), which involves simplification and economy of resources by applying similar therapeutic procedures to different EDs, will be used in this group intervention. However, the unique characteristics of the cases in each group will be taken into consideration.

Patients in the experimental group will be divided into subgroups of approximately eight patients each and will be treated by clinical psychologists specifically trained for this program. The intervention will include seven sessions (1.5 h/session) delivered over a 24-week period. The contents include the following: psychoeducation, cognitive restructuring, relaxation, behavioral training, and relapse prevention.

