#### Control Group Intervention

All patients in the control group will receive standard treatment (TAU) from their GP according to the usual criteria. In most cases, this will involve pharmacological treatment.

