### Economic Assessment

In this study, our aim was to compare the association between cost-effectiveness and cost-utility of the two treatments. The economic evaluation will be conducted by recording variables (see below) obtained from patient medical records and patient interviews.

To quantify direct costs, the following variables (only related to EDs) will be registered and assessed: number of patient consultations with psychologists and/or psychiatrists; number of patient visits to the PC centers (GP, nurse, or social worker); number of patient visits to public or private hospitals; number of visits to clinics/physicians associated with private health insurance companies; number of road traffic, workplace, or domestic accidents; number of hospitalizations and emergency room visits; medications used (name of drug, daily dose, and duration of treatment); consultations with other therapists (i.e., podiatrists, physiotherapists, and dieticians). Diagnostic tests requested by the GP and/or specialists to assess physical symptoms secondary to the emotional disorder(s) will be included. Indirect costs will include all days off from work. If a replacement worker is needed, then this will be registered as an indirect cost as well.

All the variables will be collected for the following time points: 3 months before study inclusion; at baseline; immediate post-treatment; and at 6 and 12 months post-treatment.

After providing written informed consent, the participants will be registered in the treating center. Pre- and post-treatment assessments are to be carried out using computerized self-reported screening tests. All pretreatment assessments will be performed at the treating PC center after scheduling an appointment with the clinical psychologist. A computer with Internet access is used to collect data. All data are stored on a general virtual website (surveymonkey.com). At all post-treatment follow-up assessments, the same instruments will be completed in person at the treating center.

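### The no-discounting rule rests on a 12-month study, but the plan's own schedule runs about 17.5 months from baseline

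*Protocol article*

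**What the plan says.** Four parts of the protocol article bear on the time horizon.

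- **Cost-Utility Analysis** gives the duration and the rule that follows from it: "Given that the duration of this study is only 12 months, neither costs nor outcomes are subject to discount". The ratio is "defined as the difference in mean costs divided by the difference in mean QALYS".
- **Experimental Group** gives the length of the treatment phase: "The intervention will include seven sessions (1.5 h/session) delivered over a 24-week period".
- **Clinical Evaluation** sets the visits: "Patients will be assessed at baseline, immediately after treatment finalization, and at 6 and 12 months post-treatment". **Economic Assessment** collects the cost variables for "3 months before study inclusion; at baseline; immediate post-treatment; and at 6 and 12 months post-treatment".
- **Control Group Intervention** describes usual care without a duration or an end: "All patients in the control group will receive standard treatment (TAU) from their GP according to the usual criteria".

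The article does not otherwise state the period over which costs and QALYs are to be accumulated.

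**The concern.** Twelve months is the length of post-treatment follow-up, not the span of the study. The 24-week treatment phase comes before it. A horizon longer than a year removes the only reason given for leaving costs and outcomes undiscounted.

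The sentence is also the only statement of duration in the economic analysis, so an analyst may take it as the accrual window. Costs and QALYs grow with time, and Main Outcomes lists both the economic variables and QALYs. A different window therefore gives different totals and can give a different ratio.

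A second question follows from the visit anchor. Every post-baseline assessment is timed from the end of treatment. That point is reasonably clear for a therapy course of fixed length. It is not defined for open-ended care from a general practitioner.

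**Working it through.** **Inputs from the article:** treatment phase 24 weeks (Experimental Group); last assessment 12 months after treatment (Clinical Evaluation, Economic Assessment); stated duration 12 months (Cost-Utility Analysis).

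**Assumed, not in the article:** discount rate 3% to 5% a year; utility 0.70 (range 0.6 to 0.8); 52.18 weeks per year, which is 4.348 weeks per month.

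**1. Can the 12 months be reproduced?** Three readings were tried.

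- Baseline to last visit: 24 / 4.348 = 5.52 months, and 5.52 + 12 = 17.52 months. That is about 76 weeks, or 1.46 years. It is not 12 months.
- Twelve months from the end of treatment: this gives 12 months but leaves out the 24-week phase in which the therapy sessions fall. Description of Cost Analysis prices those sessions, as part of nine assessment and treatment sessions (€39 × 9 = €351, divided by 8 patients).
- Twelve months from baseline: the window ends 12 − 5.52 = 6.48 months after treatment and leaves out the planned 12-month post-treatment visit.

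No reading of 12 months covers both the costed treatment phase and the last planned visit.

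**2. Share of the period beyond month 12:** 5.52 / 17.52 = 31.5%.

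**3. Effect of discounting on a stream spread evenly over 1.46 years.** With the first year undiscounted and the remainder divided by (1 + r), the retained fraction is [1 + 0.46/(1 + r)] / 1.46.

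- r = 3%: (1 + 0.4466) / 1.46 = 0.991, a reduction of 0.9%.
- r = 3.5%: a reduction of 1.1%.
- r = 5%: (1 + 0.4381) / 1.46 = 0.985, a reduction of 1.5%.

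Continuous discounting from month 0 is harsher and gives reductions of 2.1% (at 3%) to 3.5% (at 5%).

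**4. Conditional effect of unequal anchors.** Suppose usual-care patients were anchored at week w instead of week 24, and QALYs were accrued over each patient's actual time. The artificial difference between arms is then utility × (24 − w) / 52.18.

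| Anchor for usual care | Usual-care window (months) | Gap at utility 0.6 | 0.7 | 0.8 |
|---|---|---|---|---|
| Week 24 | 17.5 | 0 | 0 | 0 |
| Week 20 | 16.6 | 0.046 | 0.054 | 0.061 |
| Week 12 | 14.8 | 0.138 | 0.161 | 0.184 |

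Week 20 at utility 0.70 is 4 / 52.18 × 0.70 = 0.054 QALY. A later anchor gives the same size with the opposite sign. These rows show sensitivity. The article does not say that any of these anchors is used.

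**The case against.** The strongest reply is that the proven error changes little. Discounting alters totals by about 1% on the mildest assumption. It acts on both arms and moves costs and QALYs in the same direction, so much of it cancels in the ratio. That stands as a statement about size. The cancellation need not be complete, because the therapy cost falls in the first 24 weeks and would not be discounted, while later costs and benefits would be.

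A reader might infer two stronger points, and the document supports neither.

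- **That therapy costs drop out of the analysis.** Economic Assessment collects cost variables at baseline and immediately after treatment, and Description of Cost Analysis prices the sessions explicitly. The intention is plainly to count them. What is wrong is the stated duration, which does not fit that intention.
- **That the two arms have different windows and the ratio is therefore biased.** The article gives one schedule for all patients and nowhere says that usual-care visits fall at other times. The flowchart is not shown, and the full protocol of the parent trial is not at hand; either may tie usual-care visits to week 24. A gap also requires that QALYs be accrued over actual and unequal time. With nominal visit times it would not appear.

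What survives is the contradiction over duration, which does not depend on any unseen document, and an anchor that the article leaves undefined for usual care.

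**Conclusion.** The 12-month duration is wrong on the article's own figures. The schedule spans about 76 weeks (17.5 months) from baseline, about 31.5% of it beyond month 12, so the reason given for "neither costs nor outcomes are subject to discount" does not hold. This conclusion rests only on the stated treatment length and visit schedule.

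The direct consequence is small: a reduction in totals of 0.9% to 1.5% if only the part after month 12 is discounted at assumed rates of 3% to 5%, or 2.1% to 3.5% with continuous discounting from the start. These figures assume an even stream over time. The more important reason to correct the sentence is that it is the only duration given for the economic analysis, and taken literally it would exclude either the treatment phase or the final visit.

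The difference between arms is a risk and not a finding. It is about 0.05 QALY per 4 weeks of unequal anchoring at an assumed utility of 0.70, provided that QALYs accrue over actual time, and zero if usual care is matched to week 24.

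**What to change.** 1. Correct the sentence on duration in Cost-Utility Analysis.
2. State one horizon for costs and QALYs of about 76 weeks from randomisation, identical in both arms and including the treatment phase.
3. Time the assessments and cost periods of both arms from randomisation, at about weeks 24, 50 (24 + 26) and 76 (24 + 52). Record the visit dates; the article does not say that they are recorded.
4. Make the base case one in which costs and QALYs accrued after month 12 are discounted at a named rate, and report the undiscounted result as a sensitivity analysis. The article gives no rate, so one has to be chosen and justified.

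The cost is mostly wording plus slightly more analysis work. The cost period from week 50 to week 76 straddles month 12 by about 2 weeks, so a simple rule for splitting it is needed. The horizon should be fixed before the data are analysed, so that the window cannot be chosen after the ratio is seen.
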